# LABORATORY PROCEDURES

Blood samples will be used for the isolation of peripheral blood mononuclear cells (PBMCs) for cytokine stimulation and for the isolation of plasma.

PBMCs will be isolated after gradient centrifugation of whole blood over Ficoll. After serial washing, counting and exclusion of dead cells, they will be stimulated with purified ligands of SARS-CoV-2 for the production of TNFα, IL-1β, IL-6, ΙL-10, IL-17, IL-22 and IFNγ. Inflammatory mediators and suPAR will also be measured in patients’ plasma. Among measured mediators will be sIL-2R, IL-8 triglycerides and fibrinogen.

The study central lab will be the Laboratory of Immunology of Infections at the 4^th^ Department of Internal Medicine at ATTIKON University General Hospital.

# STUDY ENDPOINTS

*Primary study endpoint*

The primary study endpoint is the rate of patients who will not develop SRF (see Appendix V for definition) until day 14. Patients dying before study visit of day 14 are considered non-achieving the primary endpoint.

*Secondary study endpoints*

- Comparison of the primary endpoint with historical comparators
- Change of scoring for respiratory symptoms between days 1 and 7
- Change of scoring for respiratory symptoms between days 1 and 14
- Change of SOFA score between days 1 and 7
- Change of SOFA score between days 1 and 14
- Change of cytokine stimulation between days 1 and 7
- Change of plasma inflammatory mediators between days 1 and 7

# NUMBER OF PATIENTS

Although this is an exploratory trial, it is powered based on data from Greek patients showing that the 85.9% of those with lower respiratory tract infection by COVID-19 and suPAR≥6 ng/ml will develop SRF. To decrease this to 50% with power 80% at the 10% level of significance, sixty (60) patients need to be enrolled. Taking into consideration, the single-arm study design, 100 patients will be enrolled to make result more robust.

# STATISTICAL ANALYSIS

The primary endpoint will expressed as percentage and 95% confidence intervals. Comparisons with historical cases will be done by the Fisher exact test. Any p-value below 0.05 will be considered significant.

# ADVERSE EVENTS

Adverse events (AEs) and Serious Adverse Events (SAEs) will be collected from baseline until the last patient’s evaluation. Investigators should monitor subjects for adverse events and are responsible for recording ALL adverse events and serious adverse events occurring to a patient during the trial.

An adverse event is any undesirable medical occurrence in a subject administered a pharmaceutical product and which does not necessarily have a causal relationship with this treatment. The time relationship is defined from the moment the AE occurs during therapeutic treatment until 30 days or 5 half-lives after treatment discontinuation. The adverse event may be a sign, a symptom, or an abnormal laboratory finding.

**Serious adverse events** (SAEs) must be reported to within 24 hours. If an adverse event meets any of the following criteria, it is considered SAE:

- **Life-threatening situation** The subject was at risk of death at the time of the adverse event/experience. It does not refer to the hypothetical risk of death if the AE were more severe or were to progress.
- **Inpatient hospitalization** or prolongation of existing hospitalization.
- **Persistent or significant disability/incapacity** Any AE having an outcome that is associated with a substantial disruption of the ability to carry out normal life functions, including the ability to work. This is not intended to include transient interruption of daily activities.
- **Congenital anomaly/birth defects** Any structural abnormality in subject’s offspring that occurs after intrauterine exposure to treatment.
- **Important medical events/experiences** that may not result in death, be life-threatening, or require hospitalization may be considered a serious adverse event/experience when, based upon appropriate medical judgment, **they may jeopardize the subject and may require medical or surgical intervention to prevent one of the outcomes listed above,** i.e., death, a life-threatening adverse event/experience, inpatient hospitalization or prolongation of existing hospitalization, a persistent or significant disability/incapacity, or a congenital anomaly/birth defect. Examples of such medical events/experiences include allergic bronchospasm requiring intensive treatment in an emergency room or at home, blood dyscrasias or convulsions that do not result in inpatient hospitalization, or the development of drug dependency or drug abuse.
- **Spontaneous and elective abortions** experienced by study subject.

**A non-serious adverse event** is any untoward medical occurrence in a patient or subject who is administered a pharmaceutical product, and which does not necessarily have a causal relationship with this treatment. A non-serious adverse event is one that does not meet the definition of a serious adverse event given.

***Grading of severity***

The severity of the adverse events shall be graded as:

- **Mild** the adverse event is transient and well tolerated by the patient
- **Moderate** the adverse events causes discomfort and affects the usual activities of the patient.
- **Severe** the adverse events affects the usual activities of the patient to an important degree and may cause disability or be life-threatening.

***Relationship to the drug***

The investigator will use the following definitions to assess the relationship of the adverse event to study drug:

- **Probably Related**: The adverse event has a strong time relationship to the drug or relapses if re-induced, and another etiology is improbable or clearly less probable.
- **Possibly Related**: The adverse event has a strong time relationship to the drug and an alternative aetiology is as probable or less probable.
- **Probably not Related**: The adverse event has a slight or no time relationship to the drug and/or there is a more probable alternative aetiology.
- **Unrelated**: The adverse event is due to an underlying or concomitant disease or to another pharmaceutical product and is not related to the drug (no time relationship and a much more probable alternative aetiology).

If an investigator’s opinion of possibly related, probably not related or not related to study drug is given, an alternate etiology must be provided by the investigator. Please note that a severe adverse event/experience is not necessarily serious, as the term severe is a measure of intensity while a serious adverse event is determined based on the aforementioned regulatory criteria. Individual un-blinding thought to be necessary for the management of an adverse event will be documented in the subject Case Report Form.

# QUALITY CONTROL AND ASSURANCE

Quality control and assurance checks are performed by sponsor in order to allow periodic review of adequacy of the study activities and practices and allow for revising such practices as needed so the data and process are maintained, the study meets the protocol and procedural requirements, and is reproducible.

Before enrolling any subject in this study, sponsor personnel and the investigator have to review the protocol, the IB, the CRFs and instructions for their completion, the procedure for obtaining informed consent and the procedure for reporting AEs and SAEs.

A qualified representative of the sponsor will monitor the conduct of the study by visiting the site and by contacting the site by telephone and e-mail. During these site visits, all source documents are reviewed, and information recorded in the CRFs is verified against them.

Besides routine monitoring, quality assurance will be documented through independent auditing of the quality control activities and where applicable, by regulatory authorities through inspections.

**ETHICAL CONSIDERATIONS**

Prior to the initiation of this study, the study design will receive ethical, scientific, and where applicable, regulatory review. Investigators will conduct this study in accordance with the principles of the Declaration of Helsinki, GCP, and applicable regulatory requirements.

Regarding Informed Consent Form obtaining procedures, before any procedure specified in the protocol is performed, a subject must:

- Be informed of all pertinent aspects of the study and all elements of informed consent
- Be given time to ask questions and to consider the decision to participate
- Voluntarily agree to participate in the study
- Sign and date the updated and approved by IEC/REB ICF version.

**PROTOCOL ADHERENCE AND AMENDMENTS**

Investigators ascertain that they will apply due diligence to avoid protocol deviations. All significant protocol deviations will be recorded and reported in the clinical study report (CSR). Any change or addition to the protocol can only be made in a written protocol amendment that must be approved and signed by the sponsor, health authorities where required, and the IEC/REB.

# APPENDIX II Study visits

| **Visits days** | **Screening** | **1** | **2** | **3** | **4** | **5** | **6** | **7** | **8** | **9** | **10** | **14** |
| --- | --- | --- | --- | --- | --- | --- | --- | --- | --- | --- | --- | --- |
| Informed consent | x |  |  |  |  |  |  |  |  |  |  |  |
| Exclusion criteria | x |  |  |  |  |  |  |  |  |  |  |  |
| Inclusion criteria | x |  |  |  |  |  |  |  |  |  |  |  |
| suPAR measurement | x |  |  |  |  |  |  | x |  |  |  |  |
| Scoring of symptoms |  | x |  |  |  |  |  | x |  |  |  | x |
| SOFA score |  | x |  |  |  |  |  | x |  |  |  | x |
| Blood sampling |  | x |  |  |  |  |  | x |  |  |  |  |
| Anakinra administration |  | x | x | x | x | x | x | x | x | x | x |  |
| Trimethoprim/sulfamethoxazole  administration |  | x | x | x | x | x | x | x | x | x | x |  |
| Severe respiratory failure |  |  | x | x | x | x | x | x | x | x | x | x |
| AE/SAE |  | x | x | x | x | x | x | x | x | x | x | x |

# APPENDIX III The SOFA score

| **Variable** | **0 points** | **1 point** | **2 points** | **3 points** | **4 points** |
| --- | --- | --- | --- | --- | --- |
| PaO_2_/FiO_2_(mmHg) | ≥400 | <400 | <300 | <200 | <100 |
| Platelets (per mm^3^) | ≥150 | <150 | <100 | <50 | <20 |
| Hypotension | MAP≥ 70 mmHg | MAP<70 mmHg | Dobutamine whatever dose | Adrenaline≤0.1* or  Noradrenaline  ≤0.1* | Adrenaline>0.1* or  Noradrenaline >0.1* |
| Glasgow Coma Scale | 15 | 13-14 | 10-12 | 6-9 | <6 |
| Bilirubin (mg/dl) | <1.2 | 1.2-1.9 | 2.0-5.9 | 6.0-11.9 | ≥12 |
| Creatinine (mg/dl) or Urine output | <1.2 | 1.2-1.9 | 2.0-3.4 | 35-4.9 or <500ml/day | ≥5.0 or  <200ml/day |

*μg/kg/min

Each variable is scored between 0 and 4. The SOFA score is the sum of the score of each variable

# APPENDIX IV Scoring of respiratory symptoms

| **Symptom** | **Absent (score=0)** | **Mild (score=1)** | **Moderate (score=2)** | **Severe (score=3)** |
| --- | --- | --- | --- | --- |
| **Cough** | No cough or resolution (to pre-CAP levels) | Cough present but it does not interfere with subject’s usual daily activities | Cough present, frequent and it does interfere with some of the subject’s usual daily activities | Cough is present throughout the day and night; it limits most of the subject’s usual daily activities and sleep patterns |
| **Chest pain** | No chest pain or resolution of chest pain related to CAP | Chest pain present occasionally with deep breathing but it does not interfere with subject’s usual daily activities | Chest pain is present with normal breaths and it does interfere with the subject’s usual daily activities | Chest pain is present at rest and/or with shallow breathing; it limits most of the subject’s usual daily activities |
| **Shortness of breath (dyspnea)** | No shortness of breath or resolution (to pre-CAP Baseline) | Shortness of breath with strenuous activities only but it does not interfere with subject’s usual daily activities | Shortness of breath with usual activities and it does interfere with the subject’s usual daily activities | Shortness of breath with minimal exertion or at rest; it limits most of the subject’s usual daily activities |
| **Sputum** | No coughing up of phlegm/sputum or resolution (to pre-CAP Baseline) | Subject coughs up a small amount of phlegm/sputum | Subject coughs up a moderate amount of phlegm/sputum | Subject coughs up a large amount of phlegm/sputum |

# APPENDIX V Definition of severe respiratory failure

Presence of all of the following:

- pO_2_/FiO_2_ less than 150
- Need for mechanical or non-mechanical ventilation (CPAP)

**STATISTICAL ANALYSIS PLAN (5 October 2020)**

The study is powered for the primary endpoint making the hypothesis that 60% of patients with lower respiratory tract infection due to COVID-19 and suPAR≥6 ng/ml upon hospital admission will develop SRF. To decrease this to 45% with power of 90% at a 5% level of significance, two hundred sixty (260) patients need to be enrolled. Taking into consideration, the single-arm study design, 500 patients should be enrolled to make results more robust. Data will be analyzed for the intention-to-treat (ITT) population.

An interim analysis will be conducted after completion of the 30-day follow up of the first 130 patients, i.e. 50% of the number of patients needed to be enrolled as calculated by power analysis. Parallel comparators receiving standard-of-care treatment (SOC) will be used all patients hospitalized at the same time period in eight departments of Internal Medicine in tertiary hospitals of Athens who were participating in the registry of the Hellenic Sepsis Study Group without participating in the SAVE trial ([www.sepsis.gr](http://www.sepsis.gr)). Data and biosample collection is done in the SOC comparators after written informed consent. The same inclusion and exclusion criteria will apply in the parallel comparators under SOC as in patients participating in the SAVE trial. Data collection in these departments has been approved by the Ethics Committees of the participating hospitals. Propensity matching will be performed among comparators to the 130 patients enrolled in the SAVE trial, so as the 130 comparators will be fully comparable to all below criteria:

- Age
- Comorbidities, as expressed by the Charlson’s Comorbidity Index
- Admission severity scores namely pneumonia severity index (PSI), acute physiology and chronic health evaluation (APACHE) II score, SOFA score and WHO severity classification of COVID-19
- Co-administered treatment of azithromycin, hydroxychloroquine and dexamethasone

Primary outcome and binary secondary outcomes as well as serious adverse event and adverse event rates between the two groups will be expressed as percentages and will be compared by the Fisher exact test, calculating also the respective odds ratios. The time to an event will be compared between the two groups by survival analysis. Stepwise Cox regression analysis will be conducted for the primary outcome and 30-day mortality. Quantitative secondary outcomes will be expressed as median values with respective interquartile range and will be compared by the Mann-Whitney U test.

The cost of hospitalization will be measured by adding the itemized cost of stay, drugs, and interventions and will be expressed as median with respective interquartile range. Salaries of nurse and medical stuff will not be included. Cost comparison will be done by the Mann-Whitney U test.

Qualitative baseline characteristics will be expressed as frequencies and percentages and compared by the Fisher exact test. Quantitative baseline characteristics will be expressed as mean values with standard deviation if following a normal distribution or median values with quartiles if following linear distribution. Comparisons of quantitative baseline characteristics will be done by the Student’s t-test or by the Mann-Whitney U test respectively. Paired comparisons will be done by the Wilcoxon’s rank-signed test. Non-parametric correlations will be done according to Spearman.

Analysis will be conducted with SPSS Version 25.0. All P values will be two-sided. Any P value <0.05 will be considered as statistically significant.

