## Secondary study endpoints

- Comparison of the primary endpoint with comparators receiving standard-of-care treatment
- Change of scoring for respiratory symptoms between days 1 and 7
- Change of scoring for respiratory symptoms between days 1 and 14
- Change of SOFA score between days 1 and 7
- Change of SOFA score between days 1 and 14
- Change of Peripheral Blood Mononuclear Cells’ (PBMCs) functionality between days 1 and 7
- Change of gene expression between days 1 and 7 (transcriptional, proteomic and metabolomic analysis)
- Change of plasma inflammatory mediators between days 1 and 7
- 30-day mortality
- 90-day mortality

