# INTERIM AND STATISTICAL ANALYSIS

An interim analysis will be conducted after completion of the 30-day follow up of the first 130 patients, i.e. 50% of the number of patients needed to be enrolled as calculated by power analysis. As comparators will be used patients hospitalized with pneumonia by the SARS-CoV-2 virus in other departments of Greek hospitals in which full data collection is performed by the Hellenic Sepsis Study Group, after written informed consent. Data collection in these departments has been approved by the Ethics Committees of the respective hospitals. For the purpose of this analysis, patients receiving standard-of-care treatment (SOC) will be selected among the total patients whose data are fully collected in order to fulfill the same inclusion and exclusion criteria as patients enrolled in the SAVE trial. Propensity matching will be performed among comparators and 130 patients enrolled in the SAVE trial, so as the 130 comparators will be fully comparable to all below criteria:

- Age
- Comorbidities, as expressed by the Charlson’s Comorbidity Index
- Admission severity scores namely pneumonia severity index (PSI), acute physiology and chronic health evaluation (APACHE) II score, SOFA score and WHO severity classification of COVID-19
- Co-administered treatment, such as azithromycin and dexamethasone

The primary endpoint will expressed as percentage and 95% confidence intervals. Comparisons with historical cases will be done by the Fisher exact test. Any p-value below 0.05 will be considered significant.

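### Comparator selection and propensity matching are specified only for the 130:130 interim analysis; the plan does not say how the standard-of-care comparison is built for the final 500 patients.

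*Supplement*

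**What the plan says.** The SAP sets the interim as follows: "An interim analysis will be conducted after completion of the 30-day follow up of the first 130 patients". It explains the 130 as "i.e. 50% of the number of patients needed to be enrolled as calculated by power analysis", that figure being 260. The same paragraph names the source of the comparators ("will be used all patients hospitalized at the same time period in eight departments of Internal Medicine in tertiary hospitals of Athens", under the same eligibility criteria as SAVE) and fixes the matching: "Propensity matching will be performed among comparators to the 130 patients enrolled in the SAVE trial", giving 130 comparators.

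Protocol version 3.0, under Interim and Statistical Analysis, has the same structure. Comparators are chosen for the interim: "For the purpose of this analysis, patients receiving standard-of-care treatment (SOC) will be selected among the total patients whose data are fully collected". The matching again has a fixed size: "Propensity matching will be performed among comparators and 130 patients enrolled in the SAVE trial". A closing sentence then assigns the Fisher exact test to comparisons with historical cases and does not mention matching. The protocol synopsis also places the standard-of-care comparison in its interim-analysis row.

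Three other statements reach beyond the interim:

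- On enrolment, the SAP says that, in view of the single-arm design, "500 patients should be enrolled to make results more robust".
- The protocol lists as a secondary endpoint "Comparison of the primary endpoint with comparators receiving standard-of-care treatment", with no restriction to the interim.
- The SAP's analysis text compares the primary outcome, the secondary outcomes, adverse events, time to event and cost between two groups, without saying which patients form them.

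**The concern.** In an open-label, non-randomised study, the choice of comparators largely determines the estimated treatment effect. Here that choice is fixed for the first 130 treated patients and left open for the rest. It would then be made after the interim results are known, and several candidate analyses would be available.

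Calendar time makes this more than a missing detail. Enrolment runs for 24 months, and the documents themselves show background care changing. The protocol's Background describes hydroxychloroquine and azithromycin as the standard at the outset, while the matching list now includes dexamethasone. Calendar time is not a matching factor. Comparators matched to the first 130 patients cannot be assumed to represent the care that the later 370 would otherwise have received.

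**Working it through.** **Inputs.** Interim and matched set: 130 treated and 130 comparators (SAP and protocol). Planned enrolment: 500 (both). SRF rates: 55% v 35% (protocol, Number of Patients) and 60% v 45% (SAP). Power 90%, 5% significance, N = 260 (both). Two-sided tests (SAP).

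**1. Coverage.** 500 − 130 = 370, and 370/500 = 74% of treated patients have no planned matching. As a share of planned enrolment the interim is 130/500 = 26%. The stated 50% is 130/260.

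**2. What the 260 is.** Pooled normal formula, per arm: n = [1.96·√(2p̄(1−p̄)) + 1.2816·√(p₁(1−p₁)+p₂(1−p₂))]² / (p₁−p₂)².

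- Protocol, 55% v 35%: p̄ = 0.45; [1.96·√0.495 + 1.2816·√0.475]²/0.04 = 127.9, so 128 per arm and 256 in total (arcsine method: 258). The protocol's 260 therefore reproduces as a two-arm total. A one-sample test against 55% would need 63.
- SAP, 60% v 45%: p̄ = 0.525; [1.96·√0.49875 + 1.2816·√0.4875]²/0.0225 = 230.8, so 231 per arm and 462 in total. A one-sample test would need 114. One-sided and continuity-corrected variants do not give 260 either.

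**3. Power of the only matched comparison specified (130:130).** Power = Φ{[(p₁−p₂)·√n − 1.96·√(2p̄(1−p̄))] / √(p₁(1−p₁)+p₂(1−p₂))}.

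- Protocol rates: (0.20·11.402 − 1.379)/0.689 = 1.308, giving 90.5% (88.6% for the Fisher exact test by enumeration).
- SAP rates: (0.15·11.402 − 1.384)/0.698 = 0.467, giving 68.0% (Fisher exact 64.8%).

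**4. Precision of the risk difference.** Half-width = 1.96·√[p_c(1−p_c)/n_c + p_t(1−p_t)/n_t].

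| Treated v comparators | 55% v 35% | 60% v 45% | Matching in the plan |
|---|---|---|---|
| 130 v 130 | 11.8 points | 12.0 points | Specified |
| 500 v 500 | 6.0 points | 6.1 points | Not specified |

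The second row shows what full 1:1 matching could give. It is not a target set by either document.

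**5. The single-arm rate.** 1.96·√(0.35·0.65/n) gives 8.2 points at n = 130 and 4.2 points at n = 500. This estimate needs no comparator and does gain from the larger enrolment.

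The power and precision figures ignore within-pair correlation and residual confounding.

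**The case against.** The strongest reply is that silence is not absence. The SAP describes a concurrent registry pool wider than 130, under the same eligibility criteria, and nothing forbids rematching all 500 against it. The trial is labelled single-arm, its primary endpoint is a rate reported with a 95% CI, and the standard-of-care comparison is secondary.

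Much of this stands, and it rules out several stronger readings:

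- A reader might infer that the final analysis has no valid standard-of-care group. The documents do not support that: a usable pool is described, although its size is not given and it appears only in the interim paragraph.
- A reader might infer that all 500 will be set against the 130 interim comparators. Neither document says so.
- A reader might infer that enlarging to 500 adds nothing, or that a planned final precision is lost. Both documents tie the 500 to the single-arm design, where it does help, and neither sets a precision target for the comparison.
- A reader might infer that 130 + 130 is the full powered comparison in any case. That holds at the protocol's rates only.

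What the reply does not answer is that the SAP tests even the primary outcome between two groups. With the matching text confined to the interim, two analysts following the plan at 500 could build different groups and obtain different effects.

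**Conclusion.** The point holds as a gap in specification with consequences for bias and precision. The only matched comparison defined covers 26% of planned treated patients. A final comparison built from the text as it stands either remains at 130:130, with a half-width of about 12 points under either set of rates, or drops the matching.

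The interim label is also wrong or unsupported, depending on the rates. At 55% v 35%, the interim uses the whole of the powered two-arm comparison and not half of it. At 60% v 45%, 260 is not the required number, and the specified comparison falls well short of 90% power. Reading 260 as a two-arm total is an inference from its reproducing at the protocol's rates; neither document says so. Which pair of rates is intended cannot be settled from the documents. They must be reconciled before any power statement is made.

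**What to change.** - State in both documents that at the final analysis the propensity model is refitted and matching is redone for all enrolled SAVE patients, against eligible registry patients from the same calendar period, with calendar time in the model. Report how many treated patients are matched.
- Say explicitly which patients form the two groups in the SAP's tests at the interim and at the end. Reconcile the protocol's reference to historical cases with the SAP's parallel comparators.
- Reconcile 55%/35% with 60%/45%, say whether 260 is a two-arm total, and correct the 50% label. If the SAP's rates are kept, about 231 matched pairs are needed for 90% power, before any allowance for matching.
- If the registry cannot supply enough comparators, state that the matched comparison covers only the matched subset, give its actual power under the reconciled rates, and report the remaining patients as single-arm descriptive data.

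The cost is wording in the SAP and protocol plus a further extraction from a registry that already exists. The downside is that some treated patients may go unmatched and that the stated power may become less favourable.
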